#### Delivering PSP

All staff delivering PSP will be registered mental health professionals with some experience of working with people with personality disorders. To ensure that therapists are appropriately supported and that the needs of the participant are being met, they will meet fortnightly as part of a multidisciplinary team to discuss progress. Staff delivering PSP will be asked to complete a short proforma for every participant that they treat which records the number and length of face-to-face, telephone, and email/text contacts they have had with patients and lists the components of the intervention they delivered during the course of the treatment. Staff will also record any participants that have withdrawn early from the PSP and the reason(s) for this (if known).

#### Treatment as usual

TAU will be delivered by staff working in community mental health teams. This comprises assessment, care planning, and review. It may involve pharmacotherapy and referral to other services including access to inpatient care at times of crisis. As part of the local care pathway for people with personality disorder, staff are asked to discuss the care pathway (including discharge from secondary care) from the outset. Staff delivering TAU will be able to refer participants to longer-term psychological treatments but any patient who is already receiving psychological treatment for personality disorders at the time of the baseline assessment will not be eligible to take part in the study.

All study participants allocated to receive TAU will complete all the study assessments. Clinical teams will not be asked to complete a proforma on any usual treatment that is being delivered; instead this information will be captured in the Modified Adult Service User Schedule at baseline and six months.

### Assessments

The timing and sequence of all assessments are summarized in Fig. 1.

**Fig. 1 Fig1:**
[figure not shown]
Study assessment schedule

#### Baseline: eligibility and covariates

At baseline, we will collect demographic details and assess eligibility using the Standardized Assessment of Severity of Personality Disorder (SASPD) [32]. A score ≥ 8 on the SASPD provides a reliable assessment of the likelihood of personality disorder according to ICD-11 criteria [32]. Those who score < 8 on the SASPD will not be eligible to take part in the study. Those who are ineligible will be thanked for their time and informed of the reason(s) for this. We will also ask participants to complete the International Personality Disorder Examination (IPDE) Screening Questionnaire, a 77-item self-complete questionnaire, which provides a reliable indication of specific personality disorders using DSM-IV criteria [33]. We will use data from the IPDE to describe the range of personality problems experienced by people who take part in the study.

#### Baseline: study outcomes

Study participants will be asked to complete the following outcome measures: (1) The Work and Social Adjustment Scale (a short validated assessment of social functioning) [34]; (2) The Warwick and Edinburgh Well-Being Schedule – a seven-item questionnaire which provides a reliable assessment of mental wellbeing [35, 36]; (3) Suicidal thoughts-National Household Survey of Psychiatric Morbidity [37]; (4) the five-item EQ-5D-5 L, a reliable self-completed assessment of health-related quality of life [38] which has been shown to be sensitive to change among people with personality disorders [39]; (5) satisfaction with care will be examined using the four-item Client Satisfaction Questionnaire [40]; (6) resource use and costs will be assessed using a modified version of the Adult Service Use Schedule [41]; and (7) participants will be asked to rate any change in their mental health during the previous six months using the Clinical Global Impression Scale (CGI), a seven-point Likert scale from very much improved to very much worse [42]. Finally, participants will be asked to state how confident they are in their ability to “get yourself through difficult times and situations” on a five-point Likert scale (ranging from totally confident to totally unconfident). The psychometric properties of this item have not been tested. It was included in the study following feedback with stakeholders with lived experience of personality disorders.

#### Follow-up assessments

All study participants will complete a six-month follow-up assessment. At the six-month follow-up, the researcher will ensure that all the study outcomes that were assessed at baseline are reassessed, i.e. the Work and Social Adjustment Scale, the Warwick and Edinburgh Well-Being Schedules, suicidal thoughts and behavior using items from the National Household Survey of Psychiatric Morbidity, the EQ-5D-5 L, the Client Satisfaction Questionnaire, the Adult Service Use Schedule, patient-rated Clinical Global Impression and the five-point Likert scale on how confident they are in their ability to manage crises.

In addition to this, we will seek additional consent from study participants to take part in a qualitative interview. Following completion of the six-month follow-up interview, up to 20 participants will be invited to take part in a separate interview with a researcher with lived experience of using mental health services. During this interview, participants will be asked about their experience of taking part in the study and any steps they think we could take to improve the design of a future definitive trial. The interview will be semi-structured and guided by a topic list which will be applied flexibly. The sample for this qualitative component of the study will be purposively selected to ensure that men and women of different ages and ethnicities are selected from those in both the active and control arm of the trial. Participants from the active arm of the trial will also be selected to ensure that both those who engage and drop out of PSP are included.

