**Methods:**

A two-arm, parallel-group, single-blind, randomized controlled trial of Psychological Support for Personality (PSP) versus TAU for people aged over 18 years, who are using secondary care mental health services and have personality disorder. We will exclude people with co-existing organic or psychotic mental disorders (dementia, bipolar affective disorder, delusional disorder, schizophrenia, schizoaffective disorder, or schizotypal disorder), those with cognitive or language difficulties that would preclude them from providing informed consent or compromise participation in study procedures, and those who are already receiving psychological treatment for personality disorder. Participants will be randomized via a remote system in a ratio of PSP to TAU of 1:1. Randomization will be stratified according to the referring team and gender of the participant.

A single follow-up assessment will be conducted by masked researchers 24 weeks after randomization to assess mental health (using the Warwick and Edinburgh Well-Being Schedule), social functioning (using the Work and Social Adjustment Scale), health-related quality of life (EQ-5D-5 L), incidence of suicidal behavior, satisfaction with care (Client Satisfaction Questionnaire), and resource use and costs using a modified version of the Adult Service Use Schedule. In addition to this, each participant will be asked to complete the patient version of the Clinical Global Impression Scale.

Feasibility and acceptability will primarily be judged by study recruitment rate and engagement and retention in treatment. The analysis will focus principally on descriptive data on the rate of recruitment, characteristics of participants, attrition, adherence to therapy, and follow-up. We will explore the distribution of study outcomes to investigate assumptions of normality in order to plan the analysis and sample size of a future definitive trial.

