### Research objectives

The main objective of the study is to find out whether it is feasible to conduct a randomized controlled trial of Psychological Support for Personality (PSP) versus TAU for people in contact with mental health services who have personality disorder. The secondary objectives of the study are:To conduct a parallel-arm, single-blind, randomized trial of a psychologically informed low intensity intervention for people with personality disorder;To determine the uptake and delivery of both the low intensity intervention and TAU, including the number of sessions offered and attended;To determine the rate of recruitment, distribution of outcomes, rate of follow-up, and extent of clustering between practitioners to inform the sample size calculation for a future definitive trial;To explore service user and provider beliefs about the acceptability and design of the trial and factors that facilitate or hinder the delivery of a low intensity intervention for people with personality disorder.

If the study demonstrates feasibility, we will use the results to seek funding for a phase III randomized trial. The results of a fully powered trial would ensure that future guidelines on the use of low intensity interventions for people with personality disorder would be based on high-quality evidence, rather than having to rely solely on the expert opinion that forms the basis of current treatment guidelines.

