### Data management and analysis

Data will be entered into a password-protected Microsoft Excel spreadsheet/database held on a secure server. Study data will be archived securely and then safely destroyed after 15 years. Analysis and reporting of the trial will be in accordance with CONSORT guidelines.

Data analysis will focus principally on descriptive data on recruitment rates, characteristics of participants, attrition from the trial, non-adherence to therapy, and follow-up. The effect of treatment on outcomes will be estimated on an intention-to-treat basis using differences in scores on study outcomes and confidence intervals. We will explore the distribution of the outcomes to investigate assumptions of normality in order to plan the analysis and sample size for the definitive trial. We will also analyze the cost of the intervention using data from the proformas completed by those delivering PSP. We will also estimate costs of TAU that participants receive using data from the Adult Service Use Schedule. These data will allow us to identify the main cost components which would need to be captured in a subsequent phase, full-scale trial.

Contemporaneous notes will be made during each interview and uploaded to NVivo analytical software before thematic analysis [45]. To generate an initial coding framework, an independent thematic analysis will be conducted on a sample of transcripts and a session held to discuss and refine the thematic structure. This initial coding frame may be further refined as the analysis progresses in response to emergent themes. Supported by NVivo, the coding framework will be applied to the data (indexing) with the aim of allocating all data to a theme. Where new codes are identified, previously coded transcripts will be re-checked to ensure that extracts of data are coded consistently throughout. Full copies of notes will be retained to ensure context is maintained. The aim of the analysis will be to describe the range of experiences and responses to the intervention, highlighting any patterns and divergences in respondent accounts which support the key research questions relating to feasibility, acceptability, and optimization of both the intervention and trial design.

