### Progression criteria

Our criteria for determining the success of the feasibility study are: recruitment of at least 48 participants (80% of the target study sample of 60 participants); uptake of the low intensity intervention by at least 60% of participants in the active arm of the trial; and completion of follow-up interviews at six months by 75% of study participants. To determine the feasibility of calculating a cost analysis of health economics, we will record completion rates for the cost data and analyze them to determine what the main cost-drivers are likely to be in a full clinical trial.

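### As described, qualitative interviews are offered only after a completed six-month assessment, so the interview evidence on the trial's acceptability and design omits six-month non-completers

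*Protocol article*

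**What the plan says.** The Protocol article, Follow-up assessments, sets out the qualitative component. Consent is separate: "we will seek additional consent from study participants to take part in a qualitative interview". The invitation is placed in sequence: "Following completion of the six-month follow-up interview, up to 20 participants will be invited to take part in a separate interview". On content, "participants will be asked about their experience of taking part in the study and any steps they think we could take" to improve a later definitive trial.

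The sample is purposive on gender, age, ethnicity and trial arm, with one further rule: "Participants from the active arm of the trial will also be selected to ensure that both those who engage and drop out of PSP are" represented. That is the only drop-out criterion, and it concerns leaving the therapy.

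Under Research objectives, one secondary objective is: "To explore service user and provider beliefs about the acceptability and design of the trial". Data management and analysis directs the interview analysis at the feasibility and acceptability of both the intervention and the trial design. The Discussion adds that potential participants may dislike random allocation, and that views on this will be examined in the process evaluation.

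Other evidence on acceptability is also specified. The abstract's Methods say: "Feasibility and acceptability will primarily be judged by study recruitment rate and engagement and retention in treatment". Data management and analysis lists "recruitment rates, characteristics of participants, attrition from the trial, non-adherence to therapy, and follow-up" for descriptive reporting. Progression criteria include "completion of follow-up interviews at six months by 75% of study participants".

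**The concern.** The invitation is anchored to an event that some participants will never reach. Someone who withdraws from the trial, or who does not attend at six months, does not arrive at the step where the invitation is made, and the article describes no other way in. The rule on PSP drop-outs does not close the gap, because a person can leave therapy and remain in the trial, or leave the trial altogether.

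This matters because the interviews are the described means of learning what participants think of the trial itself: being randomised, being assessed, and what should change. People who stopped taking part are likely to have something particular to say on those questions, and follow-up is one of the criteria for going on to a definitive trial. The study will count how many were lost at six months but describes no way of asking them why.

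The Discussion also relies on the patient-rated Clinical Global Impression at follow-up, together with the qualitative data, to look for negative effects of a short intervention. As described, both of those sources miss the same people.

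**Working it through.** **Inputs (Protocol article)**
- Target sample: 60 (Sample size; Progression criteria).
- Recruitment criterion: at least 48, given as 80% of 60 (Progression criteria).
- Follow-up criterion: 75% at six months (Progression criteria).
- Maximum number invited to interview: 20 (Follow-up assessments).

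**1. The plan's own figure.** 0.80 × 60 = 48, so the recruitment criterion reproduces. There is no power calculation to check; the Sample size section says none was used.

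**2. The most non-completers the follow-up criterion tolerates.** Formula: N − (0.75 × N), with the product rounded up to a whole person where needed.
- N = 60: 0.75 × 60 = 45 completers; 60 − 45 = 15.
- N = 48: 0.75 × 48 = 36 completers; 48 − 36 = 12.
- As a share: 15/60 = 12/48 = 25%.

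**3. What this means for the interviews.** If 20 interviewees were drawn in proportion from everyone randomised, about 20 × 0.25 = 5 would be non-completers at that level of loss. Under the described sequence the number is 0. The sample is purposive and does not aim at proportionality, so the 5 is only a yardstick and not a target.

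**4. Who can reach the invitation, on the plain reading**

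| Participant | Reaches the invitation? | Counted in the quantitative feasibility data? |
|---|---|---|
| Engaged with PSP, completed six months | Yes, sampled on purpose | Yes |
| Dropped out of PSP, completed six months | Yes, sampled on purpose | Yes |
| Treatment as usual (TAU), completed six months | Yes | Yes |
| Either arm, withdrew from trial or missed six months | No stated route | Yes: attrition and follow-up, and PSP uptake and retention if in that arm |

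The gap is the last row, and only in the middle column.

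**The case against.** **The sentence may state timing rather than eligibility.** The article nowhere says that non-completers are barred, and completion is not listed among the purposive criteria. This is a fair reading, and it is why the point is put as the absence of a stated route. But the timing is tied to completing an assessment, and no alternative is given for people who do not complete it.

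**A journal article condenses the full protocol.** Recruitment details for the qualitative work may be set out there. That stands as a caution. However, the article does state the sampling rule, with its timing and criteria, and the point concerns the rule as stated.

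**Interviewing after follow-up is sensible.** Researchers are blinded, and an earlier conversation about the trial could disclose allocation or colour self-reported outcomes. The article does not give this reason, but it is a good one for anyone still to be assessed. It does not apply to people who will not be assessed.

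**Other evidence covers those who leave.** A reader might infer that trial leavers are shut out of all evidence on acceptability. The documents do not support that: acceptability is judged primarily on recruitment, engagement and retention, and leavers count in the attrition and follow-up figures. A reader might also infer that reasons for attrition are lost entirely. That too goes beyond the text: under Delivering PSP, staff record reasons for early withdrawal from PSP where known. Those records come from staff, cover one arm, and concern the therapy rather than the trial, so they narrow the gap without closing it.

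**The lack of a drop-out criterion in the TAU arm is not a separate flaw.** TAU is continuing usual care, with no trial-delivered course of therapy to leave. The only relevant loss there is leaving the trial, which is the same point.

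**Conclusion.** The point holds in a limited form. As the article describes it, participants' interview evidence on the acceptability and design of the trial comes from six-month completers, and those who withdrew from the trial or missed that assessment have no stated route in.

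The size is at most 15 of 60, or 12 of 48, if follow-up exactly meets its criterion. It would be tempting to read 15 as the expected number. The 75% is a minimum for progression, not a prediction, and better follow-up would leave fewer. Some non-completers would also be unreachable or would have refused further contact, so the number who could actually be interviewed is smaller and unknown. The 25% is not a measure of bias.

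The conclusion assumes that the sentence means what it says about sequence and that no fuller document opens another route. It does not threaten the progression decision, which rests on counts that include non-completers. It is a cheap improvement to how well a stated secondary objective is answered.

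**What to change.** Change the sampling rule as follows.

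1. Invite participants at or after the six-month time point, whether or not the assessment was completed, or at withdrawal for those who leave the trial. Limit this to people who have not withdrawn consent to contact. Anyone still to be assessed is interviewed only after that assessment, so the present order is kept for them.
2. Seek consent to be approached for interview at an existing earlier contact: baseline, or the three-month call described under Screening, baseline, and follow-up interviews. The article does not clearly say when the additional consent is taken; if it is already early, this step needs only a clarifying sentence.
3. Within the same maximum of 20, add trial non-completion in either arm as a purposive criterion, alongside the existing one for PSP engagement.
4. If no non-completers can be reached, say so as a limitation of the qualitative findings. The limitations listed in the Discussion do not include it.

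The cost is a change of wording and possibly of consent timing, with no additional interviews. The downside is that some invitations will go unanswered and a few completer places are given up. The Trial status section reports recruitment as ongoing, so later participants could still be covered.

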### Sample size

In keeping with recommendations for feasibility studies, we have not based plans for sample size on a power calculation [43]. Instead we judged that a sample of 60 participants will generate sufficient data to assess the rate of recruitment and follow-up in a single center and estimate levels of uptake and retention in therapy among approximately 30 people in the active arm of the trial.

### Assignment of interventions

After consenting to participation and completing screening assessments, people who are found to be eligible will be randomly allocated to PSP or TAU by a clinical trial manager at the Centre for Psychiatry, Imperial College London. A randomization list will be generated using the independent web-based service “sealed envelope” (https://www.sealedenvelope.com/simple-randomiser/v1/lists). Equal numbers of participants will be randomized to the two arms of the trial and stratification will occur by gender and study center. Throughout the study, the randomization list will be encrypted and held with the Trial Coordinating Office in order to keep the study researchers blind against treatment allocation. At the end of the study the randomization list will be unencrypted and placed in the Trial Master File. Equal numbers of participants will be randomized to each arm of the trial. Randomization will be stratified according to the referring team and gender of the participant.

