### Study setting

Study participants will be recruited from secondary care mental health services in London. Recruitment will be from community mental health teams, home treatment teams, and other community-based mental health services.

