### Ethics

Approval for the research has been given by the South Central Research Ethics Committee (Ref: 16/SW/0255) and from the Research and Development departments of the participating NHS Trust. We will ensure that the trial is conducted in full conformity with the current revision of the Declaration of Helsinki (last amended 13/09/2017. Version 4.0) and with the Medicines for Human Use (Clinical Trials) Regulation 2004 transposed into law from the EU Clinical Trials Directive 2001/20/EC, the EU Good Clinical Practice Directive 2005, and all current and future acts and requirements pertaining to its conduct.

Each study participant will be assigned a unique trial identification number at the start of the assessment process. This number will be written on all clinical assessment forms/datasheets and databases used to record data on study participants. A hard copy of a record sheet linking patient identity, contact details, and trial identification number for all participants will be kept at each site. It will be placed in the Investigator Site File, in a locked filing cabinet, separate from the paper Case Report Forms and other documents relating to a participant, which will be anonymized. Recorded data will be entered onto an electronic data management system that will use the trial identification number rather than the participant’s name or other information that could identify them.

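### The randomization section gives two different sets of stratification factors, and in a single-center trial they imply different randomization lists

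*Protocol article*

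**What the plan says.** The Assignment of interventions section states the stratification factors twice. The first statement is "Equal numbers of participants will be randomized to the two arms of the trial and stratification will occur by gender and study center". The last sentence of the same section is "Randomization will be stratified according to the referring team and gender of the participant". The Methods part of the abstract uses the second wording. Nothing in the article reconciles the two or defines study center as the referring team.

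On the number of centers, the Sample size section says the sample is meant to "assess the rate of recruitment and follow-up in a single center", and the Ethics section records approval "from the Research and Development departments of the participating NHS Trust", with Trust in the singular. On the number of teams, the Study setting section says "Recruitment will be from community mental health teams, home treatment teams, and other community-based mental health services" and gives no count.

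On allocation, the abstract says "Participants will be randomized via a remote system in a ratio of PSP to TAU of 1:1". The Assignment of interventions section twice promises equal numbers in the arms, the second time immediately before the sentence on referring team and gender.

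The Data management and analysis section plans a mainly descriptive analysis, with intention-to-treat differences in outcome scores and confidence intervals. It names no stratification factor.

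**The concern.** A list generated in advance can follow only one stratification scheme. The article gives two, in current operative text and within one section. This is not detail left to a fuller document, because the article does state the factors and states them inconsistently.

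Two things are at stake. The first is reporting: the article commits the trial to CONSORT reporting, and the allocation method reported has to be the one used. A reader cannot tell from this text whether referring team was balanced by design. The second is the precision attached to the between-arm differences. When randomization is stratified on a factor that predicts outcome, an analysis that ignores the factor tends to mis-state the width of the interval. Which factors a design-consistent estimate should include depends on which sentence is true. The trial is meant to inform the design of a definitive trial, so an accurate account of its randomization is part of its product.

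**Working it through.** **Inputs from the article.** Total sample 60; 1:1 allocation; one center (Sample size); one participating Trust (Ethics); several kinds of referring team, number not given (Study setting); gender as a factor in both statements, taken here as two levels. The follow-up criterion is 75% (Progression criteria).

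**The article's own figures.** 60 / 2 = 30 per arm, which agrees with its approximate figure for the active arm. 0.80 × 60 = 48, which agrees with its recruitment criterion. Neither depends on the stratification factors.

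**Number of strata** = levels of the first factor × 2 genders.

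| Scheme | Levels of first factor | Strata | Mean participants per stratum |
|---|---|---|---|
| Gender and study center | 1 (single center) | 1 × 2 = 2 | 60 / 2 = 30 |
| Referring team and gender | 2 teams (assumed) | 2 × 2 = 4 | 60 / 4 = 15 |
| Referring team and gender | 4 teams (assumed) | 4 × 2 = 8 | 60 / 8 = 7.5 |
| Referring team and gender | 10 teams (assumed) | 10 × 2 = 20 | 60 / 20 = 3 |

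With one level, center adds no strata, so the first row is gender alone. The team counts are assumptions that show the range. For any number of teams above one, the two sentences call for different lists.

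**Equal numbers.** A stratum with an odd number of participants cannot split evenly, and a stratum that ends partway through a block can be uneven too. These remainders can add up across strata. Many small strata therefore do not guarantee equal arms, whereas a 1:1 ratio is a claim the procedure can support.

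**Cost of including the factors.** If follow-up just meets the criterion, 0.75 × 60 = 45 participants contribute. With an intercept and an arm term, 45 − 2 = 43 residual degrees of freedom remain. Adding gender leaves 42. Adding k teams as well leaves 42 − (k − 1): 41 for 2 teams and 33 for 10 teams. Pooling small teams reduces the loss.

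**The case against.** The strongest case against is that this is a leftover phrase. Two of the three statements name referring team and gender, so study center is the outlier. The section repeats itself on equal numbers too, which suggests an editing slip. The list is kept and will be placed in the Trial Master File, so the scheme can be looked up. This makes team and gender the likelier scheme, but likelihood is an inference, and the text still contains an operative sentence that is wrong if that inference is right. The Ethics section's wording that a linking record "trial identification number for all participants will be kept at each site" might hint at more than one center, but it gives no number and does not displace the single-center description.

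It is also fair to say that the phrase on equal numbers is softened by the 1:1 ratio in the abstract and the approximate active-arm figure under Sample size. That part is a wording correction only.

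A reader might infer more, and the documents do not support it:

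- **That the trial cannot be analysed as stated.** The stated analysis names no stratification factor, so it can be carried out under either scheme. The article's silence on factors is not itself a fault, since such detail commonly sits in the analysis plan.
- **That leaving team out confounds the comparison.** No section says the referring team determines the content of usual care. The Treatment as usual section says community team staff deliver it and mentions one local pathway. Without team stratification, randomization still balances teams in expectation, and what remains is chance imbalance.
- **That unequal arms would do real damage.** Take 33 against 27: (1/33 + 1/27) / (2/30) = 0.06734 / 0.06667 = 1.010, and √1.010 ≈ 1.005. The standard error rises by about 0.5%. Any estimate of how often such a split would occur needs a team count and block size that the article does not give, and it would describe the team scheme rather than measure the contradiction.

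**Conclusion.** The contradiction stands. One section gives two incompatible stratification rules. In a single center the rule "stratification will occur by gender and study center" reduces to gender alone, so the two sentences describe different lists: 2 strata against 2 per referring team. The text does not show which was used. This rests on the article's own description of one center and one Trust, and on there being more than one referring team, as the Study setting section implies. The 4 to 20 strata rest on an assumed 2 to 10 teams.

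The severity is minor to moderate. This is a feasibility trial without a power calculation. Its progression criteria concern recruitment, uptake and follow-up, and none depends on the stratification factors. No stated figure changes. What needs correcting is the description of the randomization and the choice of factors that follows from it.

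**What to change.** 1. Check the list in use and state its stratification factors, once, in the Assignment of interventions section, and identically in the abstract. If the list uses referring team and gender, delete study center. If it uses gender only, say so and correct the abstract.
2. Replace both promises of equal numbers with a 1:1 allocation ratio.
3. When the between-arm differences and confidence intervals are estimated, include the factors actually used: gender, and referring team if it was used, with small teams pooled. Record this in the Data management and analysis section or the analysis plan.

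The cost is a text correction, slightly more analysis and the few degrees of freedom shown above. The Trial status section reports 50 participants recruited by the end of May 2018; their allocations are not affected.
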